#### Enrollment of LTBI Contacts

Contacts testing positive on QuantiFERON-TB Gold Plus (QIAGEN N V) will subsequently receive chest computed tomography (CT) or chest X-ray, as well as pooled sputum nucleic acid amplification testing (eg, GeneXpert MTB-RIF [Danaher Corp]) to exclude active TB. LTBI is defined as a positive interferon-gamma release assay result without evidence of active TB. Those with confirmed LTBI and aged ≥13 years are eligible for this trial. Study protocols will be thoroughly explained to eligible participants by site investigators, with written informed consent obtained prior to enrollment. Parental or guardian consent is mandatory for minors (aged <18 years). Participants meeting the inclusion criteria but declining enrollment in the TPT trial will be invited to join a supplemental nonintervention cohort. After providing separate informed consent, they will be followed for 24 months to monitor for the development of active TB. Further eligibility validations will require review of medical history and comprehensive laboratory evaluations to exclude contraindications to TPT. Textbox 1 shows the detailed inclusion and exclusion criteria.

Textbox 1.Inclusion and exclusion criteria for the TB-YOUTH study.

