### Study Objectives and End points

The primary objective is to demonstrate noninferiority of the ultrashort course of the 1H_3_P_3_ TPT regimen compared with the standard 3HR regimen in preventing active TB, as measured by the 24-month cumulative incidence of active TB following randomization. The secondary objectives include: (1) to compare safety, patient-reported quality of life, and treatment discontinuation rates attributable to AEs between the regimens; (2) to evaluate treatment adherence using protocol-defined completion criteria; (3) to assess acquired *M tuberculosis* drug resistance among participants who develop active TB after TPT; and (4) to establish a contemporary nonintervention cohort for exploratory comparison, delineating the natural progression to active TB among individuals with high-risk LTBI in whom active TB has been ruled out.

The primary end point is a composite of bacteriologically confirmed or clinically diagnosed active TB within 24 months after randomization. Bacteriologically confirmed active TB refers to *M tuberculosis* identification via ≥1 sputum culture and/or molecular assay (eg, GeneXpert MTB-RIF) with detectable bacterial load. Clinically diagnosed TB combines objective clinical symptoms (≥2 of the following: cough ≥2 weeks, fever, night sweats, weight loss >10%, or hemoptysis) and imaging findings highly suggestive of active TB (eg, cavity or nodular lesions on chest CT), after exclusion of alternative diagnoses. Secondary end points include severity-graded AEs, treatment discontinuation (defined as any permanent cessation prior to regimen completion), treatment completion (defined as completing ≥90% of scheduled doses within 110% of the planned treatment duration), all-cause mortality, and acquired drug resistance determined by drug susceptibility testing or targeted molecular assays of *M tuberculosis* isolates from active TB cases. Exploratory analysis will use the nonintervention cohort to establish the background incidence of active TB, against which the risk reduction of each TPT regimen can be calculated. Patient-reported outcomes (PROs) will be calculated using health state utility values and EuroQol visual analog scale scores.

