### Statistical Analysis

Statistical analyses will be performed using SAS and R (R Foundation for Statistical Computing). Multiple imputation will be conducted to handle missing data, with additional inverse probability weighting applied for the nonintervention cohort to adjust for potential attrition bias. Continuous variables will be summarized as mean (SD) or median (IQR), as appropriate. Categorical variables will be summarized as counts and percentages.

The primary analysis will assess the noninferiority of the 1H_3_P_3_ regimen compared to the 3HR regimen in preventing active TB over the 24-month follow-up period, and the primary end point is the composite of bacteriologically confirmed or clinically diagnosed active TB. To account for the cluster randomized design and the inherent correlation within clusters, we will use a Cox proportional hazards regression model with shared frailty terms and exact likelihood estimation. Noninferiority of the 1H_3_P_3_ regimen relative to the 3HR regimen will be concluded if the analysis demonstrates that the 1H_3_P_3_ regimen does not experience a ≥20% relative reduction in protective efficacy for preventing active TB over the 24-month follow-up period. To enhance precision and address potential baseline imbalances despite randomization, the model will adjust for key prespecified covariates, such as age, sex, BMI, characteristics of the index case (smear or cavitation status), and cluster size. Outcomes will be assessed via 2 prespecified analyses with explicit definitions: the modified intention-to-treat population includes all randomized participants who received at least 1 dose of the study medication, analyzed by the assigned treatment group regardless of subsequent protocol deviations or treatment discontinuation; the per-protocol population includes all randomized participants who completed ≥90% of scheduled doses within 110% of the planned treatment duration without major protocol deviations (including use of prohibited concomitant anti-TB medications, enrollment despite exclusion criteria, or unblinding to outcome assessors). Prespecified subgroup analyses will examine treatment effect heterogeneity by age (13-17 years vs ≥18 years) and index case features (smear or cavitation status), tested through interaction terms in Cox models (interaction *P*<.10).

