For secondary end points, all AEs, serious AEs (SAEs), and treatment discontinuations due to AEs will be documented. Group differences in AE proportions will be analyzed using the chi-square test or Fisher exact test (2-sided *α*=.05). Treatment completion is defined as consuming ≥90% of planned doses within 110% of the planned treatment duration (≥11 doses within 6 weeks for the 1H_3_P_3_ group and ≥81 doses within 16 weeks for the 3HR group). The 2-year cumulative incidence of active TB in the nonintervention cohort will be calculated using the Kaplan-Meier method, with 95% CI estimated. The protective efficacy of the 1H_3_P_3_ and 3HR regimens relative to the nonintervention cohort will be quantified as the risk reduction rate: 1–(intervention group incidence/nonintervention group incidence). The Fisher exact test will be used to compare incidence differences among the 3 cohorts.

All analyses concerning the PRO end point will be explicitly restricted to the subgroup of participants who complete the EuroQol 5-Dimensions 3-level questionnaire. The baseline characteristics of this PRO subgroup will be compared between the 2 arms to confirm that randomization balance was maintained. Any interpretation of PRO findings will explicitly acknowledge their exploratory nature and the fact that they are derived from a subset of the total study population. Trends in PRO metrics over time will be visualized using line graphs, with mean values and 95% CIs plotted to illustrate group-level changes. A mixed-effects model for repeated measures will be used to compare PRO differences between the 1H_3_P_3_ and 3HR groups across time points, with fixed effects including treatment group, assessment time point, treatment group×time point interaction, age, sex, BMI, and index case cavitation status, and a random participant-specific intercept to account for within-subject correlation from repeated assessments.

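### The Fisher exact test named for the three cohorts does not match the regimen-specific efficacy it accompanies: as one test it cannot say which regimen differs from nonintervention, and in any form it ignores censoring, weights and clustering

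*Protocol article*

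**What the plan says.** In the protocol article, Study Objectives and End points lists among the secondary objectives "to establish a contemporary nonintervention cohort for exploratory comparison". It then says that the exploratory analysis will use this cohort to "establish the background incidence of active TB, against which the risk reduction of each TPT regimen can be calculated". Under Enrollment of LTBI Contacts, the cohort is formed as follows: "Participants meeting the inclusion criteria but declining enrollment in the TPT trial will be invited to join a supplemental nonintervention cohort".

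Statistical Analysis gives the methods:

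- The 2-year incidence in the nonintervention cohort is estimated by Kaplan-Meier with a 95% CI.
- Each regimen's efficacy "will be quantified as the risk reduction rate: 1–(intervention group incidence/nonintervention group incidence").
- Missing data are handled by multiple imputation, with "additional inverse probability weighting applied for the nonintervention cohort to adjust for potential attrition bias".
- The primary comparison of the two regimens uses a Cox model with shared frailty, to account for clustering.
- For the three cohorts together: "The Fisher exact test will be used to compare incidence differences among the 3 cohorts".

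The article does not say whether this last sentence means one 3×2 test or several 2×2 tests. It names no other test of a regimen against nonintervention.

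**The concern.** The efficacy question has two parts: does 1H3P3 differ from nonintervention, and does 3HR differ from nonintervention? The sentence on the Fisher test most naturally describes a single test over three groups. Such a test rejects whenever any pair differs. One of those pairs is 1H3P3 versus 3HR, which is the primary model's question and not a question of efficacy against no treatment.

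There is also a mismatch of method that does not depend on how the sentence is read. The plan estimates nonintervention incidence from censored data, adds weights against attrition in that cohort, and recognises correlation within clusters. Fisher's test takes unweighted integer counts from independent individuals. The p-value and the efficacy estimate would then describe different quantities.

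At stake is how the trial's only concurrent comparison with no preventive treatment is interpreted.

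**Working it through.** **Inputs from the document** (Randomization and Sample Size Calculation)

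- Incidence without treatment: 7% at 2 years.
- Assumed efficacy of both regimens: 70%, so 0.07 × (1 − 0.70) = 0.021, the article's 2.1%.
- Evaluable participants per arm: 396 clusters × 4 = 1584. With 10% attrition, 1584 / 0.9 = 1760, as stated.
- ICC 0.05 and mean cluster size 4.

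**Assumptions**

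- The size of the nonintervention cohort is not given. It was varied over 200, 400, 800 and 1584.
- Two-sided α = 0.05. The article states this for adverse events; here it is assumed for the Fisher test too.

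The article gives no operating figure for the three-cohort test, so there is none to reproduce.

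**Step 1: what one 3×2 test responds to.** The exact 3×2 test (Freeman-Halton, full enumeration) and pairwise Fisher tests were simulated with independent observations. There were 300 trials per cohort size for the first two rows and 500 for the third. Ranges are over the four cohort sizes.

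| True incidence: 1H3P3 / 3HR / nonintervention | 3-cohort p<0.05 | 1H3P3 vs nonintervention p<0.05 | 3HR vs nonintervention p<0.05 |
|---|---|---|---|
| 7% / 2.1% / 7% | 100% | 3–6% | 91–100% |
| 2.1% / 7% / 7% | 100% | 91–100% | 3–6% |
| 2.1% / 2.1% / 7% | 89–100% | 91–100% | 91–100% |

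The 3-cohort result looks alike whether one regimen works, the other works, or both do. The pairwise tests separate these cases, with essentially the same power when both regimens work.

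**Step 2: one data set.** Take 111/1584 events (7.0%) in 1H3P3, 33/1584 (2.1%) in 3HR and 56/800 (7.0%) in nonintervention.

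- 3-cohort test: p = 1.9 × 10⁻¹².
- 1H3P3 versus nonintervention: p = 1.0.
- Estimated efficacy of 1H3P3: 1 − (111/1584)/(56/800) = 1 − 0.0701/0.0700 = −0.1%.
- Estimated efficacy of 3HR: 1 − 0.0208/0.0700 = 70%.

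**Step 3: clustering.** The design effect is 1 + (4 − 1) × 0.05 = 1.15. An unadjusted test statistic is inflated by this factor, so in large samples:

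- 3-cohort (chi-square, 2 df): P(χ² > 5.991/1.15) = exp(−5.991/2.30) = 0.074.
- Pairwise: P(|Z| > 1.960/√1.15) = P(|Z| > 1.828) = 0.068.

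Simulation with all three incidences at 2.1% and ICC 0.05 (1500 trials per cohort size, clusters of 4 in all three cohorts) gave 6.9–7.5% for the 3-cohort test, in line with the formula. For the pairwise test it gave 4.6–6.4%. With so few events the exact pairwise test is conservative (3.1–5.6% without clustering), and this offsets part of the inflation. The 6.8% is therefore a large-sample figure, and the loss of error control in the pairwise test is small.

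**Step 4: the methods side by side.**

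| Element of the plan | Can a Fisher test use it? |
|---|---|
| Kaplan-Meier incidence (censoring) | No: it needs a count of events and non-events |
| Inverse probability weights | No: weighted counts are not integers |
| Correlation within clusters | No: it assumes independent individuals |

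This holds for one 3×2 test and for pairwise tests alike.

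**The case against.** **The sentence may mean pairwise tests.** It speaks of differences in the plural and follows two regimen-specific efficacy ratios, and a condensed article may leave such detail to an analysis plan that is not shown. This stands: the document does not say that a single test is meant. It answers the first half of the point only, because pairwise Fisher tests still cannot use the planned estimator, the weights or the clustering.

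**No efficacy conclusion is tied to the p-value.** Efficacy is estimated separately and the comparison is labelled exploratory. In the example above, the 1H3P3 estimate of about 0% would itself reveal the failure, and the primary noninferiority analysis would address a gap between 7% and 2.1%. This stands and limits the consequence.

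A reader might infer more than the document supports, in four ways.

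- *That the 100% is a false-positive rate.* It is not. The three incidences do differ in that scenario, so rejecting their equality is correct; the figure is power. It would mislead only if read as evidence on 1H3P3 versus nonintervention, and the article does not say it will be read so.
- *That the nonintervention data hardly count in the 3-cohort test.* With 2.1%, 2.1% and 7%, that cohort alone differs, and the test still rejects in 89% of trials with only 200 in it.
- *That attrition will distort the Fisher test by a known amount.* Any such figure depends on a loss rate not in the document and on scoring lost participants as event-free, whereas the plan provides for multiple imputation and weighting.
- *That the absence of a stated interval for the efficacy ratios is an error.* A condensed article may leave this out.

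**Conclusion.** The point holds in limited form. The named test does not fit the quantity it accompanies. As a single 3×2 test, its natural but not its only reading, it cannot show which regimen differs from nonintervention. On either reading it conflicts with the plan's own Kaplan-Meier estimate, attrition weights and allowance for clustering. The loss of error control from clustering is modest: about 7.4% (3-cohort) or at most about 6.8% (pairwise) at nominal 5%, given ICC 0.05 and clusters of 4 in every cohort. The size of the nonintervention cohort is assumed; the 100% in the 7% / 2.1% / 7% scenario did not change from 200 to 1584.

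Only an exploratory analysis is affected. The primary noninferiority comparison and the sample size do not depend on this test. Nor would a better test make the comparison with nonintervention fully valid: that cohort is made up of people who declined the trial, and the weights described address attrition, not the choice to decline.

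**What to change.** Replace the sentence on the Fisher test as follows:

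1. Name two contrasts: 1H3P3 versus nonintervention, and 3HR versus nonintervention.
2. For each, report protective efficacy as 1 minus the ratio of 24-month Kaplan-Meier incidences, using the planned attrition weights for the nonintervention cohort. Give a 95% CI from a cluster-robust variance or a bootstrap that resamples clusters.
3. Drop the 3-cohort Fisher test, and leave 1H3P3 versus 3HR to the primary model.
4. State that the nonintervention cohort consists of people who declined the trial, so both contrasts are nonrandomised and may be confounded.

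This changes a few lines of the analysis section and needs no new data or participants. By the article's account, analysis begins only after the 2-year follow-up, so the change can still be made beforehand. The cost is two exploratory intervals in place of one p-value, with slight multiplicity in an analysis already labelled exploratory.

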### Follow-Up and Assessments

Participants in both study groups will undergo prospective monitoring comprising two phases: (1) on-treatment assessment (from enrollment to 1 month after treatment completion) and (2) posttreatment assessment (up to 24 months after randomization). On-treatment assessments will involve standardized clinical evaluations, including physical signs, laboratory testing, medication adherence (pill counts and self-reporting), and safety monitoring, and will be scheduled at week 2, month 1, and month 2 for the 1H_3_P_3_ arm, and at week 2, then monthly until month 4 for the 3HR group. On the basis of recommendations from the independent protocol review board, and to comprehensively evaluate the impact of interventions on quality of life, a protocol amendment was implemented after approximately 2300 participants had been enrolled. Following ethics committee approval, the EuroQol 5-Dimensions 3-level questionnaire (version 6.0, December 2018) was incorporated as an exploratory end point. This questionnaire will be administered at every on-treatment assessment for participants enrolled after the amendment’s effective date. Posttreatment assessment will focus on active TB surveillance as well as delayed AE monitoring and will occur every 6 months from randomization until study exit. At each visit, participants will receive a standardized symptom screening for active TB, including persistent cough (≥2 weeks), fever, night sweats, weight loss, hemoptysis, or other TB-associated symptoms. Participants with positive symptom screens will undergo confirmatory sputum culture and molecular diagnostic testing. The end point adjudication committee will determine the final active TB diagnosis per predefined criteria.

The schedule of this study is summarized in Table 2.

**Table 2. T2:** SPIRIT (Standard Protocol Items: Recommendations for Interventional Trials) diagram showing enrollment, intervention, and assessment procedures.

	Enrollment	Allocation	Postallocation phase						Closeout
Time point^a^	–30 days	0 day	2 weeks	1 month	2 months	3 months	4 months	Every 6 months	24 months
Enrollment									
Eligibility screening	✓								
Informed consent	✓								
Medical history	✓								
Allocation		✓							
Interventions									
1-month isoniazid plus rifapentine 3 times weekly regimen		↔^b^	↔	↔					
3-month daily isoniazid plus rifampicin regimen		↔	↔	↔	↔	↔			
Assessments^c^									
Demographic characteristics and medical history	✓	✓							

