### Randomization and Sample Size Calculation

Enrolled LTBI participants linked to the same index case will be defined as a cluster [14,15], with an assumed average cluster size of 4 participants. Cluster-level randomization will be triggered when ≥1 eligible participant is enrolled within a cluster. Randomization sequences will be pregenerated by the study statistician using SAS (version 9.4; SAS Institute Inc) and will not be accessible to any personnel involved in enrollment, assignment, or intervention delivery. Designated personnel will perform centralized randomization via the interactive web response system. Randomization results will be relayed to the respective site investigators. This is an open-label study, and all participants within the same cluster will receive identical group assignments. To address intercenter heterogeneity, a 2-stage randomization strategy will be applied: in the first stage, stratification by study site will balance baseline characteristics across centers; in the second stage, permuted block randomization (block size=4) within each site will ensure immediate group balance during participant enrollment.

On the basis of surveillance data from China’s National Tuberculosis Control Program, we estimate that the 2-year cumulative active TB incidence among LTBI participants will be 7% [16,17]. Both the 3HR and 1H_3_P_3_ regimens are assumed to have 70% protective efficacy (ie, reducing the 2-year cumulative incidence of active TB into 2.1%).

The intracluster correlation coefficient (ICC) was incorporated into calculations. A systematic review reported ICC values of 0.028 (range 0.0005‐0.21) for school-based clusters [15], while the National Institutes of Health Pragmatic Trials Collaboratory suggested a range of 0.01 to 0.05 [18]. Therefore, we adopted a conservative ICC estimate of 0.05 for this study.

Using these parameters and a prespecified noninferiority margin of a 20% relative reduction in protective efficacy, a total of 396 clusters (n=1584 participants) per treatment arm are required to achieve 80% power at a 1-sided *α*=.05. This sample size is calculated to satisfy the clinically meaningful noninferiority margin, accounting for the cluster randomized design (ICC=0.05, average cluster size=4). Accounting for a 10% attrition rate to mitigate the impact of loss to follow-up on statistical power and outcome validity, each arm will enroll 1760 participants.

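### The quality-of-life analysis is limited to participants who complete the questionnaire, which selects on something seen only after randomization, and 'complete' is not defined

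*Protocol article*

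**What the plan says.** The EuroQol questionnaire (EQ-5D-3L) came in by amendment. Under Follow-Up and Assessments, "a protocol amendment was implemented after approximately 2300 participants had been enrolled", and the questionnaire became an exploratory end point. The same section says who receives it: "This questionnaire will be administered at every on-treatment assessment for participants enrolled after the amendment’s effective date".

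The on-treatment visits "will be scheduled at week 2, month 1, and month 2 for the 1H_3_P_3_ arm", which makes three. The control arm has five: "at week 2, then monthly until month 4 for the 3HR group". The phase is described as "on-treatment assessment (from enrollment to 1 month after treatment completion", but the first visit listed in either arm is week 2.

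Statistical Analysis then says that all patient-reported outcome analyses will be "explicitly restricted to the subgroup of participants who complete the EuroQol 5-Dimensions 3-level questionnaire". It plans to compare the arms' baseline characteristics in that subgroup, in order to confirm that the balance from randomization was kept. It also requires any interpretation to state that the findings are exploratory and come from a subset of the trial. The model is a repeated-measures mixed model with a random participant intercept. The same section gives multiple imputation as the general approach to missing data.

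Study Objectives and End points lists patient-reported quality of life under the secondary objectives.

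**The concern.** Being enrolled after a calendar date does not depend on how a participant responds to treatment. Returning a questionnaire at week 2 or later can. The trial is open-label, and Table 2 (note c) requires on-treatment visits to be attended in person. The Introduction attributes low adherence and completion of 3HR in China to its length and toxicity, and reports pilot completion above 90% for 1H3P3. Tolerability could therefore affect both the quality-of-life score and whether a participant is in the analysis at all. A comparison of the arms among completers would then no longer be fully protected by randomization.

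The baseline check does not repair this. It compares measured characteristics recorded before treatment, whereas the selection of interest acts through experience on treatment. Two completer groups can match on age, sex and BMI and still differ in how many participants with poor tolerance have left each of them.

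The word 'complete' is also open. It could mean one form, all scheduled forms, or the form at a given visit, and these readings give quite different analysis sets.

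**Working it through.** The article gives no sample size, power or return rate for this end point, so there is no stated figure to reproduce.

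**Inputs from the article**
- Scheduled questionnaires for 1H3P3: week 2, months 1 and 2, so k = 3 (Follow-Up and Assessments).
- Scheduled questionnaires for 3HR: week 2, months 1, 2, 3 and 4, so k = 5 (same section).
- Planned enrollment: "each arm will enroll 1760 participants", so 2 × 1760 = 3520 (Randomization and Sample Size Calculation).
- Enrolled when the amendment took effect: about 2300.

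**Assumption, not in the article**
- Probability p that a scheduled form is returned: 0.80 to 0.98, equal in both arms and independent across visits.

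**Step 1. Who is eligible.** 3520 − 2300 = 1220 participants, or 1220/3520 = 35% of the trial, if the target is met. An even split gives about 610 per arm.

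**Step 2. All scheduled forms required.** Inclusion is p^k.

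| p | 1H3P3 (p³) | 3HR (p⁵) | Gap, percentage points |
|---|---|---|---|
| 0.80 | 51.2% | 32.8% | 18.4 |
| 0.90 | 72.9% | 59.0% | 13.9 |
| 0.95 | 85.7% | 77.4% | 8.4 |
| 0.98 | 94.1% | 90.4% | 3.7 |

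Gaps are taken before rounding. At p = 0.95, about 14% of 1H3P3 and 23% of 3HR would be left out. Of 610 per arm that is about 87 and 138 participants (610 × 0.143 and 610 × 0.226).

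**Step 3. One form is enough.** Inclusion is 1 − (1 − p)^k. At p = 0.80 this is 1 − 0.2³ = 99.2% for 1H3P3 and 1 − 0.2⁵ = 99.97% for 3HR. The gap is under 1 point and slightly favours inclusion of 3HR. At higher p it is smaller still.

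**Step 4. When membership is settled.** On either reading it depends on forms collected from week 2 onward, because no earlier questionnaire visit is listed. The selection is therefore made after randomization under both rules; only its likely size differs.

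**Step 5. Does the model need the restriction?** No. A repeated-measures mixed model uses participants with some forms missing, so complete sets are not required.

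**The case against.** The strongest reply is that the sentence means something harmless. The questionnaire arrived after about 2300 enrollments, so some wording was needed to separate participants with data from those never given the form. The questionnaire is named in the singular, the next sentences speak of a subset of the trial, and the model is built for repeated measurements. All of this fits a reading of at least one form. On that reading the imbalance between arms is negligible. The proposed set would also give almost the same mixed-model estimate, since a participant with no form contributes nothing to the likelihood unless missing forms are imputed. How many forms count is, besides, a detail often left to an analysis plan, and the end point is called exploratory.

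Much of this stands, and it limits the point. It does not remove it. The restriction is a stated rule that a later analysis plan would inherit, it rests on post-randomization behaviour on either reading, and the baseline check is given a purpose that it cannot serve.

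Four stronger readings are tempting and are not supported:
- *The two sections contradict each other.* Follow-Up and Assessments says who is given the form; Statistical Analysis says whose data are analysed. The second group is nested in the first, and no rival analysis set is defined.
- *The plan requires 5 forms of 3HR and 3 of 1H3P3.* These are the scheduled numbers. Nothing says that all must be returned.
- *The result will be biased toward no difference.* Nothing in the article fixes a direction.
- *The completer rule lets in people who join a cluster once its arm is known.* That possibility comes from randomizing a cluster when its first member is enrolled, so it concerns the whole trial and not this sentence.

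**Conclusion.** The concern holds as a minor one. The quality-of-life set is defined by an event that occurs after open-label treatment starts, with the key word undefined, and the baseline comparison offered in support cannot exclude selection on tolerability. The possible difference between arms in inclusion runs from under 1 percentage point (one form enough) to about 8 points at 95% return and 14 at 90% (all forms required). These figures rest on assumed return rates that are equal in the arms and independent across visits; actual return could differ by arm. They describe who is included and do not measure bias in utility or visual analogue scores, whose size and direction are unknown. The conclusion about timing rests on the listed schedule. If the full protocol has a day-0 form, a rule of at least one form could be met before treatment, while a rule of all forms could not. The exploratory label keeps the severity low, although quality of life also appears among the secondary objectives.

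**What to change.** In Statistical Analysis, replace the restriction to completers with a set defined by eligibility: all participants enrolled after the amendment's effective date, analysed in the assigned arm, with every available questionnaire entered in the mixed model. Make the baseline comparison in that full set. Report questionnaire return by arm and visit, so that a reader can judge how much is missing and whether it differs between regimens.

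Leaving out late members of clusters randomized before the amendment may be run as a sensitivity analysis. It would address late joining only in part, since late members of clusters randomized after the amendment would remain.

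The cost is a sentence or two of analysis wording and one table of return rates. No visit, form or participant is added. By the end of December 2025 the trial had enrolled 2478, about 178 beyond the 2300 at which the amendment came in, and analysis waits for the end of the 2-year follow-up, so the change can be made before the analysis starts.
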